## Abstract

**Background:**

Low back pain (LBP) is a major health issue associated with considerable health loss and societal costs. General practitioners (GPs) play an important role in the management of LBP; however, GP care has not been shown to be the most cost-effective approach unless exercise and behavioural counselling are added to usual care. The Fear Reduction Exercised Early (FREE) approach to LBP has been developed to assist GPs to manage LBP by empowering exploration and management of psychosocial barriers to recovery and provision of evidence-based care and information. The aim of the Low Back Pain in General Practice (LBPinGP) trial is to explore whether patients with LBP who receive care from GPs trained in the FREE approach have better outcomes than those who receive usual care.

**Methods/design:**

This is a cluster randomised controlled superiority trial comparing the FREE approach with usual care for LBP management with investigator-blinded assessment of outcomes. GPs will be recruited and then cluster randomised (in practice groups) to the intervention or control arm. Intervention arm GPs will receive training in the FREE approach, and control arm GPs will continue to practice as usual. Patients presenting to their GP with a primary complaint of LBP will be allocated on the basis of allocation of the GP they consult. We aim to recruit 60 GPs and 275 patients (assuming patients are recruited from 75% of GPs and an average of 5 patients per GP complete the study, accounting for 20% patient participant dropout). Patient participants and the trial statistician will be blind to group allocation throughout the study. Analyses will be undertaken on an intention-to-treat basis. The primary outcome will be back-related functional impairment 6 months post-initial LBP consultation (interim data at 2 weeks, 6 weeks and 3 months), measured with the Roland-Morris Disability Questionnaire. Secondary patient outcomes include pain, satisfaction, quality of life, days off from work and costs of care. Secondary GP outcomes include beliefs about pain and impairment, GP confidence, and actual and reported clinical behaviour. Health economic and process evaluations will be conducted.

**Discussion:**

In the LBPinGP trial, we will investigate providing an intervention during the first interaction a person with back pain has with their GP. Because the FREE approach is used within a normal GP consultation, if effective, it may be a cost-effective means of improving LBP care.

**Trial registration:**

Australian New Zealand Clinical Trials Registry, ACTRN12616000888460. Registered on 6 July 2016.

**Electronic supplementary material:**

The online version of this article (doi:10.1186/s13063-017-2225-8) contains supplementary material, which is available to authorized users.

## Background

Low back pain (LBP) is a highly prevalent and expensive health condition [1–4]. At any given point in time, 18% of the world’s population may be experiencing LBP, and 38% of people will experience LBP over the course of 1 year [5]. Back pain is one of the leading causes of health loss globally and in New Zealand [6, 7].

Back pain has been estimated to cost 2% of gross domestic product in developed countries [3, 4]. Health care use represents about 15% of the total societal cost of LBP, with the majority of costs due to absence from work and decreased productivity [2]. Consequently, interventions that promote early return to work and that minimise lost productivity are likely to have the greatest impact on the societal burden of LBP [2].

Back pain is a very common reason to visit general practitioners (GPs), both internationally and in New Zealand [1, 8, 9]. People are more likely to seek care when they have high levels of disability and/or pain [10, 11]. Although GP care is cheaper than other treatments for LBP, authors of a systematic review found that it is generally less cost-effective when costs associated with loss of earnings and changes in productivity are taken into account [12]. However, when exercise and behavioural counselling were added to usual GP care, it became the most cost-effective approach [12].

Factors that predict persistent LBP-related activity or work limitation include high initial levels of pain and impairment, psychiatric co-morbidities, low health status and a range of psychosocial factors [13, 14]. Low pain self-efficacy beliefs, poor expectation of recovery, elevated fear avoidance beliefs, catastrophisation, psychological distress (anxiety, depression and stress) and reliance on passive coping strategies have all been found to be independently associated with poor disability outcomes [15–23]. Those who have more maladaptive beliefs, particularly higher levels of fear or more catastrophic beliefs, are also more likely to seek care [10, 24, 25].

The Fear Reduction Exercised Early (FREE) approach was developed in New Zealand to assist GPs manage LBP [26]. This complex intervention includes GP training, electronic consultation support and patient information resources. Its aim is to empower GPs to explore and address psychosocial barriers to recovery and provide evidence-based care and information to their patients with LBP. FREE may be delivered by a GP at the first consultation a person has for an episode of acute LBP or during subsequent LBP consultations. Researchers found in pilot testing that the FREE approach was acceptable to GPs and considered to be useful [26]. The aim of this study is to explore whether patients with LBP who receive care from GPs who are trained in the FREE approach have better outcomes than those who receive usual care.

## Methods/design

### Aim

The primary objective of the Low Back Pain in General Practice (LBPinGP) Study is to measure the effectiveness of the FREE approach versus usual care for LBP in terms of reduction in back-related functional impairment. Secondary objectives are to (1) measure the effectiveness of the FREE approach versus usual care for LBP in terms of reduction in pain and increase in health-related quality of life and patient satisfaction; (2) measure the cost-effectiveness of the FREE approach and usual care over a period of 6 months from societal, health system and Accident Compensation Corporation (ACC; a New Zealand government controlled universal accident insurance scheme) perspectives; and (3) consider which elements of the intervention mediate any observed changes in health outcomes. In sensitivity analysis, we will explore these same outcomes for new episodes of acute LBP (defined as less than 6 weeks’ duration with no LBP-related care received during the preceding 3 months) to explore the study’s initial hypothesis that FREE will be most effective when received at the first consultation for an episode of acute LBP.

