##### Inclusion/exclusion criteria

This study will include patients aged 18 years and over who present to a participating GP with LBP of any duration as their primary complaint. Patients will not be eligible if they have had back surgery in the last 6 months, have been unable to do their normal work (or normal daily activities for those who are retired, unemployed or work at home) for more than 3 of the last 6 months, have LBP due to a non-back-related condition (e.g., cauda equina compression, inflammatory arthritis, malignancy, infection, aortic stenosis or aneurysm), have a concomitant health condition which means they are not suitable for trial participation (e.g., pregnancy or major psychological disturbance), or are unable to read and write in English.

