### Statistical analysis

Statistical significance will be judged with an α of 0.05. All results will be reported as estimates of effect size (e.g., mean difference, risk ratio, number needed to treat [NNT]) with 95% CI. All analyses will be conducted on an intention-to-treat basis.

Analyses will also account for clustering of data as appropriate. For the patient-level outcomes, this clustering will be specified at the GP level using random effects specifying the GP. Whereas randomisation is at the practice level, clustering effects on outcome values are expected to be driven mostly by inter-practitioner variability. For the GP-level outcomes, clustering will be specified at the practice level. The stratified randomisation will be handled by including the practice size stratum identifier in analytical models (less than or equal to eight FTE GPs, more than eight FTE GPs).

In most instances, analysis will be conducted using linear mixed models (for continuous numerical outcomes such as the RMDQ) or generalised linear mixed models (for categorical outcomes such as satisfaction levels). These models allow for inclusion of data from between baseline and the final endpoint to better estimate the differences at the main endpoint in the presence of missing follow-up data [60]. These models will be adjusted for important baseline covariates (age, sex, socioeconomic status, current back pain duration and nature [constant or episodic], receipt of recent or ongoing non-GP health care for back pain, previous history of back pain, baseline disability and baseline psychological factors [pain self-efficacy and recovery expectations]) [61]. The analysis will also be adjusted for baseline Health Care Providers’ Pain and Impairment Relationship Scale (HC-PAIRS) scores as measured at the level of the GP (as a measure of baseline treatment competence). We will analyse categorical outcomes using generalised linear mixed models (conditional treatment estimates) and generalised estimating equations (marginal treatment estimates) for each outcome: The former approach is to be considered the primary analysis for that output because the conditional treatment effect estimates relate to expected gains for each patient [60, 62].

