### Sample size

For 80% power to detect a between-group difference of 2.5 RMDQ points (the minimal clinically important difference) at 6 months, assuming SD of 6.0 [67] at a *p* value < 0.05 significance level, an individually randomised trial would require 91 patients per group. This has been inflated to 110 patients per group after adjustment for GP cluster effects (assuming a GP intra-cluster correlation coefficient at a conservative 0.05 and, on average, five patients per GP completing the trial). We aim to recruit 275 patient participants to allow for 20% loss to follow-up.

This design requires 22 GPs per study arm. To account for potential zero recruitment by some GPs, we will recruit 30 GPs per study arm. To further account for patient loss to follow-up (assumed ~ 20% of patients per GP) we will ask GPs to recruit seven patients. This gives a maximal potential sample size of 210 patients per study arm if all GPs recruit an average of 7 patients (total sample size = 60 GPs, 420 patients). Sample size calculations were performed using Stata 12 software (StataCorp, College Station, TX, USA).

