### Limitations

FREE was initially planned to be delivered during the first consultation which someone receives for an episode of acute LBP, and this study was designed to explore the effect of FREE in this population. The study population was expanded to include people with LBP of any duration for two reasons. Firstly, presentation rates of eligible patients to the first recruitment sites was unacceptably low and indicated that recruitment targets would not be met within time frames that were acceptable to either participating practices or the project budget. Secondly, feedback from participating GPs indicated that these restrictive recruitment criteria excluded most of the patients with LBP they commonly saw. Consequently, the generalisability of study findings was likely to be limited. The revised recruitment criteria are similar to those used in previous LBP primary care research [67]. A sensitivity analysis of the main outcomes will be performed restricted to the original study population of participants with acute LBP.

GPs will complete baseline measures post-randomisation (but prior to receiving training). Training requires that all participating GPs in a practice attend a 4-h training session together. Although it would be preferable to have all GPs complete baseline measures prior to randomisation, this is not possible, given the lead-in time required to schedule and co-ordinate training sessions with the practices. GPs will be aware of whether they will receive training, but they will not be aware of the content of the intervention when they complete baseline measures. It is possible that knowledge of group allocation could affect GPs’ responses when completing baseline measures; however, it is considered more important that these be completed close to when training is received and patients are recruited. GP measures are not the trial’s main outcome, and patients are recruited while blind to group allocation.

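### The acute-only analysis estimates the effect in the originally intended population, but it cannot inform the stated hypothesis that FREE works best there; a treatment-by-acute contrast should be added

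*Protocol article*

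**What the plan says.** Eligibility in the protocol article covers adults who "present to a participating GP with LBP of any duration as their primary complaint" (Inclusion/exclusion criteria), so acute patients are only part of the sample.

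The Aim section then states: "In sensitivity analysis, we will explore these same outcomes for new episodes of acute LBP", where a new acute episode is "defined as less than 6 weeks’ duration with no LBP-related care received during the preceding 3 months". The purpose given in the same sentence is to explore the study's initial "hypothesis that FREE will be most effective when received at the first consultation for an episode of acute LBP".

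The Limitations section explains that the trial was first planned for acute first consultations and was widened because too few eligible patients presented and because GPs found the criteria too narrow. It adds: "A sensitivity analysis of the main outcomes will be performed restricted to the original study population of participants with acute LBP".

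In Statistical analysis, back pain duration appears only in the list of baseline covariates for adjustment. The article mentions no product of arm and acute status, no estimate in the remaining patients and no contrast between the two groups.

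**The concern.** The stated purpose is comparative and the stated method is not. Whether FREE is most effective in new acute episodes depends on the difference between two effects, one in acute patients and one in the rest. The planned analysis supplies only the first.

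Set beside the all-patient result, it still gives no valid contrast, because the acute patients are part of the all-patient estimate. A significant acute-only result can arise when the effect is the same in everyone, and a non-significant one can arise merely from the smaller sample.

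The widened eligibility makes this matter. If the overall result is null or small, readers will ask whether a benefit in acute patients was diluted. As written, the plan gives them no estimate that answers the question.

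**Working it through.** **The protocol's own figures.** Sample size states: "For 80% power to detect a between-group difference of 2.5 RMDQ points", with SD 6.0. Statistical analysis states: "Statistical significance will be judged with an α of 0.05", taken here as two-sided.
- Individual randomisation: n = 2 × (1.96 + 0.842)² × 6² / 2.5² = 90.4, so 91 per group.
- Design effect: 1 + (5 − 1) × 0.05 = 1.2; 91 × 1.2 = 109.2, so 110 per group.
- Dropout: 220 / 0.8 = 275.

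All three stated figures reproduce, so these inputs are used below.

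**Assumption.** The acute share f is not in the document. I take f = 0.3 to 0.5 of 220 completers, equally split between arms and varying at random within GP. Gains from covariate adjustment and repeated measures are ignored.

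**SE of the acute-only effect.** With 5 completers per GP, an acute patient shares a GP with 4f other acute patients on average, so the design effect is about 1 + 4f × 0.05.
- f = 0.3: √(4 × 36 × 1.06 / 66) = 1.52
- f = 0.5: √(4 × 36 × 1.10 / 110) = 1.20

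A generalised least squares calculation (44 GPs, 5 completers each, ICC 0.05, SD 6) gives about 1.53 and 1.20, which I use from here.

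**SE of the interaction.** Acute and other patients share GPs, so the GP effect largely cancels and a design effect near 1 applies.
- f = 0.3: √(4 × 36 × (1/66 + 1/154)) = 1.77
- f = 0.5: √(4 × 36 × (1/110 + 1/110)) = 1.62

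Generalised least squares gives the same values. Putting the full 1.2 on every term would give 1.62 and 1.25 for the acute-only SE and 1.93 and 1.77 for the interaction SE, which overstates the imprecision by about 4-10%.

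**What the acute-only result shows if there is no effect modification.** Let the true effect be 2.5 points in both strata.
- Chance that the acute-only result is significant: Φ(2.5/1.53 − 1.96) = 37% at f = 0.3; Φ(2.5/1.20 − 1.96) = 55% at f = 0.5. An interaction test would be significant 5% of the time.
- All-patient SE: √(4 × 36 × 1.2 / 220) = 0.89. With no effect modification, the gap between the acute-only and all-patient estimates has SE of about √(SE²acute − SE²all): √(1.53² − 0.89²) = 1.25 at f = 0.3 and √(1.20² − 0.89²) = 0.81 at f = 0.5. The two estimates would differ by more than 1 RMDQ point, in either direction, about 42% and 22% of the time.

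**What the interaction could show.** Power for a 2.5-point difference in effect is Φ(2.5/1.77 − 1.96) = 29% at f = 0.3 and Φ(2.5/1.62 − 1.96) = 34% at f = 0.5. The difference detectable with 80% power is 2.80 × SE, or about 5.0 and 4.5 points.

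**Wider range.** For f = 0.2 to 0.7, generalised least squares gives an interaction SE of about 1.6 to 2.05 and an acute-only SE of about 1.0 to 1.9. The reasoning does not change.

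**The case against.** The strongest reply has five parts.

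- **The verb is explore.** No test, significance rule or subgroup conclusion is promised. This stands: a reader might infer that effect modification is to be tested, or that significance in the subset will be read as proof of it, and the document says neither. Exploring a comparative hypothesis still needs a comparison.
- **The original question is answered.** Limitations says the trial was designed to explore the effect of FREE in the acute population, and the restricted fit estimates exactly that, with less precision. This stands. A reader might infer that the trial can no longer answer the question it was designed for; the text does not support that. Only the comparative part of the hypothesis goes unaddressed.
- **The label is defensible.** Re-running the main outcomes under the original criteria checks whether conclusions depend on the widened eligibility. That may fairly be called a sensitivity analysis.
- **The detail may lie elsewhere.** The article is condensed and the SAP is not shown, so an interaction could be specified there. But the article itself names the hypothesis, the subset and the analysis meant to address it. The point is the mismatch between stated purpose and stated method, not an omitted detail.
- **The remedy is weak.** Power is low, and the interaction compares kinds of patient (acute and untreated against a mix of longer-lasting and recently treated pain) rather than the timing of delivery. Both limits are real. They call for cautious reporting; they do not turn a one-stratum estimate into a comparison.

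**Conclusion.** The concern holds in a limited form. The acute-only analysis is valid for the originally intended population, but followed as written it cannot inform whether FREE works better in new acute episodes than in other patients. The primary objective, primary analysis and sample size are untouched.

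Under the assumed 30-50% share, the acute-only 95% CI would be about ±2.4 to ±3.0 points (1.96 × 1.20 and 1.96 × 1.53), and the CI for the difference between strata about ±3.2 to ±3.5 (1.96 × 1.62 and 1.96 × 1.77). Both exceed or come close to the protocol's minimal clinically important difference of 2.5 points. The mismatch itself depends on none of these figures; only its size does.

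**What to change.** Keep the acute-only fit, described as the analysis of the original study population.

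Add to the planned linear mixed model, fitted to all patients, the acute-new-episode indicator and its interaction with arm, set up so that the contrast is estimated at 6 months. Report the RMDQ effect in acute patients, the effect in the remaining patients, and their difference, each with 95% CI. Label this a pre-specified exploratory effect-modification analysis and fix it before the allocation codes are broken. State that it compares patient groups and does not isolate the timing of delivery.

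In the Aim, tie the hypothesis about where FREE is most effective to this contrast and not to the restricted fit. If the SAP already contains such a contrast, only the wording of the Aim needs aligning.

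The cost is small: a few model terms and no new data, since the planned restriction already needs the same variable. The downside is imprecision. A non-significant interaction must not be read as evidence that the effect is the same in both groups.

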### Design

This study is a cluster randomised controlled superiority trial comparing the FREE approach to usual care for LBP management with investigator-blinded assessment of outcomes. The Standard Protocol Items: Recommendations for Interventional Trials (SPIRIT) checklist is available as an Additional file 1.

### Setting of the study

This study will be based in one geographical region of New Zealand that has a population base of 144,550 people. Compared with the New Zealand general population, the study population has a slightly higher proportion of Māori and Pacific people as well as similar proportions of people in each level of socioeconomic deprivation [27]. Patients will be recruited from general practice clinics in this region, which has a total of 21 practices.

### Participants

#### General practices

Up to ten general practices will be recruited from the study region. Practices in the region which have more than three full-time equivalent (FTE) GPs will be invited to participate in the trial in collaboration with their primary healthcare organisations (PHOs). Practices will not be invited if the PHO considers that trial participation will place an unacceptable burden due to other factors. Recruitment will not be feasible in practices smaller than three FTE GPs, given the low relative incidence of LBP presentations. Practices will enter the trial in pairs because sequential participation of practices will permit close contact with practices to optimise patient recruitment. The sequence of participation will be planned in collaboration with practices to enable simultaneous recruitment from pairs of intervention and control practices that are of similar size.

#### General practitioners

GPs will be invited to participate if they are registered medical practitioners working at a general practice in the study region that has consented to participate in the trial. GPs will be excluded if they have participated in pilot testing of the FREE approach. GP flow through the trial is presented in Fig. 1. GPs invited to participate will receive a participant information sheet. Written informed consent will be obtained by members of the research team.

**Fig. 1 Fig1:**
[figure not shown]
General practitioner (GP) trial process. *FTE* Full-time equivalent

#### Patients

##### Screening

All patients presenting to participating GPs with a primary complaint of LBP will be screened for participation by a research nurse following a brief explanation of the study. Patients meeting all inclusion criteria and no exclusion criteria will be eligible for enrolment. Patients will be enrolled and complete baseline surveys before they see their GP. Patient flow through the trial is presented in Fig. 2.

